### Quality control and data monitoring

2.10

All investigators, research assistant and onsite pharmacy technician will be required to undergo training prior to the trial to guarantee consistent practice. The training will include understanding of inclusion/exclusion/exit criteria, follow-up procedures, and completion of questionnaire and CRF. The trial will be monitored by quality assurance personnel from the research management office of the College of Medicine, University of Lagos, who will be independent from the study team, and an independent steering committee. There will be a periodic monitoring to guarantee accuracy and quality throughout the study period. The essential documents (consent information, enrolment, protocol deviations, number and proportion of missed visits, and losses to follow-up) will be monitored and checked for accuracy and completeness by the monitors. The principal investigator (PI) is responsible for the overall project and for organizing steering committee meetings. An independent steering committee will be responsible for ensuring the overall safety of participants, coordinating study meetings, supervising the study, monitoring data safety, and overseeing quality control.

### Ethics and dissemination

2.11

The study protocol was approved by the Health Research and Ethics Committee of the Lagos University Teaching Hospital on September 30th, 2018 with approval number ADM/DCST/HREC/APP/2438 [Additional file 1]. Participants will provide written informed consent [Additional file 2] prior to participation in the trial and the participant will keep a signed copy of the consent form for future references. Participants below the age of 18 years will be regarded as emancipated minors. ‘Emancipated minor’ is a person that is not of legal age to give consent (below 18 years of age in Nigeria) for a research study but who by marriage, pregnancy, being the mother of a child whether married or not or has left home and is self-sufficient can be allowed to do so legally. The trial will be reported in line with the Standard Protocol Items: Recommendations for Interventional Trials (SPIRIT) checklist [Additional file 3] and the results will be disseminated in peer review scientific journals.

## Discussion

3

Selenium is a non-metallic chemical element of great important to human health. Biochemical selenium deficiency has been associated with increased mortality among those infected with HIV and with accelerated HIV disease progression. This study aims to assess the effects of giving routine antenatal selenium supplementation to HIV-infected pregnant women on their pregnancy outcome and HIV-disease progression. If it is found to be significantly effective and safe, this trial will provide a basis for prescribing this antioxidant to HIV-seropositive women in pregnancy.

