### Confirmatory outcome variables

2.6

Primary endpoints – Preterm birth (delivery before 37 completed weeks of pregnancy) and low birth weight in term neonates (baby's birth weight less than 2.5 kg).

Secondary endpoints – HIV disease progression (change in CD4 + cells count, viral load and stage of the disease); mid-trimester miscarriage, change in haemoglobin levels; adverse events (AE) such as hepatotoxicity, gastrointestinal disturbances, dermatologic effects (nail and hair loss and dermatitis), and neurotoxicity; and perinatal mortality (number of stillbirths and neonatal deaths in the first week of life).

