#### Sample size

2.7.1

Using the data from our previous study,^[11]^ we propose to enrol 148 participants in the study to investigate the effect of selenium supplementation on the primary endpoints. The study is powered for a 2-sided test with a Type I error rate of 5% and 95% power, that is, Z_α_ = 1.96 and Z_β_ = 1.64, adjusted for a 20% drop-out rate. We also propose to enrol 180 participants to detect an effect size of 0.3 of selenium supplementation on the major secondary endpoint (reduction in HIV disease progression). This is powered for a 2-sided test with a Type I error rate of 5% and 80% power, that is, Z_α_ = 1.96 and Z_β_ = 1.64, adjusted for a 20% drop-out rate. Therefore, a total sample size of 180 is used in this study with 90 HIV-infected women randomised into each of the trial arms to assess the effects of selenium supplementation on the primary and secondary outcome variables.

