### Statistical analyses

2.8

The intention-to-treat principle will be used in the final analyses. Statistical analyses will be carried out using SPSS version 23.0 for Windows (Armonk, NY: IBM Corp.). The associations between any 2 groups of continuous variables will be tested using the independent sample or paired *t* test (normal distribution) or the Mann-Whitney *U* test (skewed data) and that of 2 groups of categorical variables with chi-square or Fishers exact test where appropriate. A series of multivariable analyses using binary logistic regression model will also be carried out to identify and control for several possible confounders of the primary and secondary outcome variables. Statistical significance will be defined as *P* < .05.

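### The Discussion ties prescribing to a finding of safety, but the only stated analysis of binary harms is a difference test at P < .05, which at this size cannot show safety for uncommon harms

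*Protocol article*

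**What the plan says.** All references are to the protocol article.

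- **Section 3 (Discussion)** sets out what a positive trial would support: "If it is found to be significantly effective and safe, this trial will provide a basis for prescribing this antioxidant to HIV-seropositive women in pregnancy". The word *safe* is not defined there or elsewhere.
- **Section 2.6 (Confirmatory outcome variables)** lists the harms among the secondary endpoints: mid-trimester miscarriage, then "adverse events (AE) such as hepatotoxicity, gastrointestinal disturbances, dermatologic effects (nail and hair loss and dermatitis), and neurotoxicity; and perinatal mortality". No expected rate or tolerable excess is given for any of them.
- **Section 2.8 (Statistical analyses)** assigns chi-square or Fisher exact tests to categorical variables and adds binary logistic regression for the primary and secondary outcomes. It closes with a single criterion: "Statistical significance will be defined as *P* < .05".
- **Section 2.7.1 (Sample size)** bases the size on the two primary endpoints and on an "effect size of 0.3 of selenium supplementation on the major secondary endpoint", namely HIV disease progression. The result is that "a total sample size of 180 is used in this study with 90 HIV-infected women randomised into each of the trial arms", a figure "adjusted for a 20% drop-out rate". Harm does not enter the calculation.
- **Sections 2.5.1, 2.9 and 2.10** provide for discontinuation of individual participants and for oversight by the ethics committee and an independent steering committee. They give no numerical rule for judging the trial's safety result.

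**The concern.** A difference test can give evidence of harm. It cannot give evidence that harm is absent, because a large P value is compatible both with no effect and with too little information. The Discussion needs a verdict of safety before the trial can support prescribing, and the analysis section offers only difference tests for the yes/no harms.

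If a non-significant result came to stand for safety, fewer women and more drop-out would make that verdict easier to reach. Imprecision would then favour the conclusion. Most is at stake for uncommon but serious outcomes such as perinatal death, where a doubling could go unnoticed in a trial of this size.

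**Working it through.** **Inputs from the article.** 180 women, 90 per arm; 20% drop-out, so 180 × 0.80 = 144, or 72 per arm; two-sided 5% level; chi-square or Fisher exact test.

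**Assumed inputs.** The article gives no harm rates, so control rates of 2%, 5%, 10% and 20% are tried, each with a doubling on selenium. Each harm is treated as yes/no per woman.

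**1. Where 180 comes from.** With the printed "Z_α_ = 1.96 and Z_β_ = 1.64" and the effect size of 0.3: (1.96 + 1.64)² / 0.3² = 12.96 / 0.09 = 144, and 144 / 0.80 = 180. The stated total is reproduced from the HIV-progression effect size alone, and no harm rate is used. (This is a one-sample formula with the Z value for 95% power, although the text labels it 80%. That is a separate matter and does not affect what follows.)

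**2. Power to detect a doubled harm rate.** Sum P(X = x) · P(Y = y) over all outcomes with more events on selenium and P < .05, where X and Y are binomial with n per arm. Fisher exact first, uncorrected chi-square in brackets:

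| Control vs selenium | 90 per arm | 72 per arm |
|---|---|---|
| 2% vs 4% | 3% (10%) | 2% (9%) |
| 5% vs 10% | 17% (24%) | 12% (21%) |
| 10% vs 20% | 40% (47%) | 32% (39%) |
| 20% vs 40% | 80% (84%) | 70% (76%) |

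Up to a control rate of 10%, every entry is below 50%. Fisher power passes 50% at a control rate of about 12.5% with 90 per arm (51%) and about 15% with 72 per arm (51%).

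**3. A worked result.** Take 10/90 events on selenium and 5/90 on placebo, a doubling. Fisher P = 0.28, so the test is not significant. The risk difference is 11.1 − 5.6 = 5.6 points. Wilson limits are 6.15% to 19.26% for 10/90 and 2.40% to 12.35% for 5/90. The Newcombe limits are then

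- lower: 5.56 − √[(11.11 − 6.15)² + (12.35 − 5.56)²] = 5.56 − 8.41 = −2.9 points;
- upper: 5.56 + √[(19.26 − 11.11)² + (5.56 − 2.40)²] = 5.56 + 8.74 = +14.3 points.

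The P value alone hides that an excess of 14 points is not excluded. With 5/90 on placebo, 13/90 on selenium still gives P = 0.08; it takes 14/90 to fall below .05.

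**4. Could another analysis of 180 women show safety?** The size needed to exclude a doubling (margin equal to the control rate p, equal true rates, one-sided 2.5%, 80% power) is n = (1.96 + 0.84)² · 2p(1 − p) / p² per arm. This gives 770 at 2%, 299 at 5%, 142 at 10% and 63 at 20%. The first three exceed 90; the last does not. Even with no events among 90 women, the upper limit of a two-sided 95% interval for the rate is 1 − 0.025^(1/90) = 4.0%.

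**The case against.** Two stronger readings are tempting, and the article supports neither.

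- **That the plan has a rule equating non-significance with safety.** It has none. Section 3 leaves *safe* undefined, and in its sentence *significantly* may govern only *effective*. Section 2.8 defines significance for tests; it does not define safety. The inference is natural, because no other statistical criterion is stated, but it remains an inference.
- **That a doubling of harm would usually be missed, whatever the harm.** This depends on rates the article does not give. Gastrointestinal disturbances, for instance, may be common; from a control rate of 20%, a doubling is found with 70% to 84% power, depending on the test and on drop-out.

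It can also be said that an article condenses a fuller protocol or analysis plan, which may specify intervals or a margin. That is fair, and the absence of such detail is not the point here. Likewise, the safety case does not rest on these tests alone: the article cites an upper intake level and literature for the dose, and provides for safety oversight. Finally, the Discussion sentence looks ahead and is not a formal decision rule, and a trial of this size can seldom settle uncommon harms.

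What remains is that the published conclusion makes a safety finding a condition for prescribing. By step 4, no unseen analysis detail would let 90 women per arm exclude a doubling with 80% power at control rates up to about 10%. Oversight and a literature-based dose rationale do not supply a criterion for the trial's own result.

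**Conclusion.** The point holds for uncommon harms. The article links prescribing to a result that is both effective and safe, states only difference tests at P < .05 for the binary harms, and sizes the trial for other endpoints. With an assumed control rate up to about 10%, a doubling would be missed more often than not under either test and at either sample size: Fisher power is 3% to 40% at 90 per arm and 2% to 32% at 72. For common events it would usually be detected.

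The figures rest on assumed control rates and on each harm being analysed as yes/no; a harm measured on a continuous scale would behave differently. This is an improvement worth making to the analysis text and the wording of the conclusion. It does not affect the validity of the efficacy comparison.

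**What to change.** In section 2.8, state that each safety endpoint (each adverse event type, miscarriage, perinatal mortality) will be reported as counts by arm and as a risk difference, selenium minus placebo, with a 95% confidence interval, for example Newcombe. Add that a non-significant test will not be taken as evidence of safety.

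In section 3, limit the conclusion to efficacy, and describe safety by the largest excess risk that the interval does not exclude.

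This takes two or three sentences and needs no extra data or participants. The article reports that recruitment had not begun at submission. The intervals do not add information that 180 women cannot give; they make the limit visible. The small downside is that the trial can no longer declare selenium safe for uncommon harms.

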### Trial status

3.1

At the time of initial manuscript submission, recruitment is yet to commence into the trial. Participants’ enrolment will start in September 2018, and the last woman is expected to be included in the trial in February 2019. The manuscript reports protocol version 2.0 (30th June 2018).
